| PRIMARY OBJECTIVES  To determine how well the expert cancer research community, in the aggregate, can forecast the overall replication rate of high impact preclinical cancer studies and the reproducibility of specific high impact basic and preclinical cancer experiments.  To determine how well individual experts in this community can forecast the overall replication rate of high impact preclinical cancer studies and the reproducibility of specific high impact basic and preclinical cancer experiments. |
| SECONDARY OBJECTIVES   1. What are the cognitive characteristics of the experts who update more appropriately? 2. Determine whether beliefs about the pace of progress in medical research (AKA medical boomster / doomster scale score) correlates with forecast skill. 3. Determine demographic characteristics of better forecasters. 4. Determine target study features (in vivo vs. in vitro, etc) with higher forecast success rates 5. How well do forecasters update after seeing results? 6. What are the demographic characteristics of experts who update more appropriately? 7. What types of evidence do the most effective forecasters prioritize, and what study features are easiest to predict? 8. Combine several above results to identify which trial and forecaster characteristics lead to more accurate forecasts. 9. Determine whether researchers who originate a report are more or less accurate than independent experts, individuals associated with the team replicating the experiment and non-experts. |
| METHOD OVERVIEW  We will use both ‘binary’ forecast methodologies (i.e. subjective probability on binary outcomes) to collect forecasts for individual replication studies, and ‘simplified continuous’ elicitations on select studies. When replication studies close, we will collect study outcomes, determine forecast scores using a proper scoring rule (called Brier score), and collect updated forecasts. |

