| PRIMARY ANALYSIS  We will calculate the Brier scores of each individual forecaster, and present a distribution. A Brier score is a proper scoring rule – meaning it incentivizes honest reporting of subjective beliefs – which measures the accuracy of a forecast: BS = 1/N $\sum_{i=1}^{N} \left( f_{i}-o_{i} \right)^{2}$ where *f_i_* is a forecast and *o_i_* is a realized outcome for each of i events.[12] We will decompose into calibration = 1/N $\sum_{i=1}^{N} {1/n_{i}\left( f_{i}-\bar{o}_{i} \right)}^{2}$, and discrimination = 1/N $\sum_{i=1}^{N} 1/n_{i}(\bar{o}_{i}\left( 1-\bar{o}_{i} \right))$.[13] We will construct calibration curves for individual forecasters. Our null hypothesis is that mean Brier score 95% confidence intervals exclude Brier score for a matched sample size of hypothetical forecasters predicting same trials using a random number generator. We will also measure the Brier Skill Score for individuals: BSS = 1 – BS/BS_ref_ where BS_ref_ is the base rate for the reference class or of a confidence interval. The sample variance can be used when is BS_ref_ unknown.[14]  Primary endpoint   1. Replicability rate measures: The brier scores for aggregate measures will be slightly higher than .25 (note: .25 is the equivalent of a 50-50 prediction meaning “I don’t know” or a random guess). The mean forecaster will perform slightly worse than base-rates. Forecasts will be skewed toward predicting more successful replications than observed, but less than statistically expected. The order of successful predictions of aggregate replicability rates will be: 2. Effect sizes at least as large (Brier of about .20 to .25) 3. Significance (p-values) (Brier of about .25)   An a priori power analysis suggests we need a sample size of 34 to detect if expert Brier scores are different than a constant (e.g. random guessing (BS = .25) or a base rate (e.g. 80% of significant effects in cancer phase 3 trials favor the new treatment[15]) by a moderate degree (difference from a constant of Cohen’s d = .5) assuming power = .80 and alpha = .05.   1. Individual study measures: The Brier scores for individual studies will be slightly lower than .25. Forecasts will predict more successful replications than observed. Brier scores will be lower (forecasts will be more successful) for forecasting the direction of the difference between effect sizes (Outcome2) compared to forecasting significant differences (Outcome1). Base-rates will outperform the typical forecaster, but aggregating the top-tier of forecasters will beat base-rates. |

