| SECONDARY ANALYSIS ON FORECAST SKILL^[[4]](#footnote-4)^  An a priori power analysis suggests we need a sample size of 34 per group to detect if detect if the experts differ from (d = .5) the novice group assuming power = .80 and alpha = .05, and we need about 180 total respondents to detect a moderate difference (f = .25) between all four strata. As analysis is exploratory, we do not intend to correct for multiple hypothesis testing.   1. Expert strata analysis: 2. The order of predicted replication rates will be: 3. Novices/Non-experts (Should be optimistic since and less attuned to the “replicability crisis” across scientific disciplines) 4. Originators (if available- should be optimistic due to their investment in these results, but more realistic than novices) 5. Independent Experts (Should be less biased due to independence from findings) 6. Replicators (if available- theoretically well attuned to flawed research design and practices) 7. The order of forecast skill will be: 8. Independent Experts (should have sufficient expertise and less biased by own work) 9. Originators (if available- should have sufficient expertise, but more myside bias) 10. Replicators (if available- assumes lab skills are higher than knowledge for this group) 11. Novices/Non-experts (assuming expertise and forecast skill are related, they have the least expertise) 12. The order of variability in forecasts will be: 13. Novices/Non-experts (assuming expertise and forecast skill are related, there should be more variability for those with the least knowledge) 14. Independent Experts 15. Replicators (if available- assumes replicators are well attuned to good and bad study design and difficulty of carrying out certain studies) 16. Originators (if available- assuming expertise and forecast skill are related, there should be less variability in recognizing real empirical relationships and flawed study design by those who have devoted their lives to studying these topics) 17. Expertise will have an inverse U-shaped (∩) relationship with forecasting success. People with low expertise will perform poorly due to inadequate information, and people with high expertise will perform poorly due to maladaptive beliefs (e.g. confirmation bias). The correlation between perceived expertise and Brier score will be ranked as follows:      1. Originators (if available- should perform when they claim higher expertise; have motivation to honestly claim high expertise for some, but not all topics) 2. Independent Experts (may be less discriminating in expertise ratings than originators since they don’t have personal relationships with any of the studies) 3. Replicators (if available) 4. Novices/Non-experts (should have consistently low expertise ratings) 5. Predictors of Forecast Skill: We will test the relationship between each demographic and scale variables and Brier Skill Score, secondarily looking at components of calibration and discrimination. The individual differences should influence the forecasts in the following order (from most to least influential). 6. More extreme updaters: Those who update more extremely relative their will have more accurate forecasts^[[5]](#footnote-5)^. 7. Pace of progress: Those who believe medical technology should progress quickly (slowly) will have more optimistic (pessimistic) forecasts. 8. Evidence reliance: 9. Those who rate the methodology of the replication attempt as important will be pessimistic. 10. Those who cite specific trial outcomes as evidence will be worse forecasters, and those who cite treatment or disease type (base rates) will be better forecasters. 11. Expertise: Those will high (self-reported and actual) expertise will be more accurate; actual expertise (H- & M-indices) will be more predictive of forecasting skill. 12. Confidence will be weakly correlated with forecasting skill. We expect a hard-easy effect where forecasters are overconfident on hard items and underconfident on easy items. 13. Demographics     1. We will also test methods of identifying forecasting skill early (prior to target event realization) the relationship between individual forecaster’s Brier scores and their average squared distance to the median compared to other baselines (mean, expectation due to chance, expectation due to base rates if available) - we hypothesize that this will lead to a strong relationship with forecast skill. 14. Aggregation of Forecasts 1: We will test whether different aggregation approaches give better forecast performance (i.e. lower Brier scores). First, to determine the relative value of using combined forecasts to make decisions, we will construct a curve of showing the relationship between Brier scores and number of aggregated forecasts. Specifically, the curve will reflect n=0 aggregation (i.e. average Brier scores of individual forecasters); n=1 (i.e. average Brier score when two forecasters forecasts are randomly aggregated); n=4 (i.e. average Brier score when 5 randomly selected forecasts are aggregated); and n=9 (i.e. average Brier score when 10 randomly selected forecasts are aggregated). We will also use transformations to make predictions more extreme.[16,17] 15. Predictors and Aggregation: Using individual differences and demographic variables that show low skill identified in step 1, we will test the competitiveness of aggregated low skill forecasters with the individual scores of high skill forecasters. For instance, suppose we find a relationship between high M-index and high forecast skill. We will then test whether, if we combine forecasts from 2, 3, 5 and 10 low M-index forecasters, on average the forecast outperforms the average forecast of high M-index forecasters.   After we have completed forecast scoring, we will also rank all individual forecasters by their Brier skill scores, and randomly select individuals within tiers of upper, middle, and lower thirds. We will test whether combined forecasts of 2, 3, 5 and 10 “low skill” forecasters can, on average, beat the forecast of randomly selected individuals from each skill tier. Brier scores will be used; as well, they will be decomposed into discrimination and calibration. |

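### Two predictions about how optimistic forecasts will be (pace of progress, importance of replication methodology) have only an accuracy score, Brier Skill Score, named as their response

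*Protocol*

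**What the plan says.** In the Protocol, Secondary Analysis on Forecast Skill, the item Predictors of Forecast Skill fixes the response for the whole family of predictors: "We will test the relationship between each demographic and scale variables and Brier Skill Score, secondarily looking at components of calibration and discrimination". Ordered predictions follow. Two concern the direction of the forecasts:

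- Pace of progress: "Those who believe medical technology should progress quickly (slowly) will have more optimistic (pessimistic) forecasts".
- Evidence reliance, first part: "Those who rate the methodology of the replication attempt as important will be pessimistic".

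The second part of evidence reliance concerns accuracy: "Those who cite specific trial outcomes as evidence will be worse forecasters, and those who cite treatment or disease type (base rates) will be better".

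Secondary objective 2 also concerns accuracy: "Determine whether beliefs about the pace of progress in medical research (AKA medical boomster / doomster scale score) correlates with forecast skill".

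The Primary Analysis section defines the score: "We will also measure the Brier Skill Score for individuals: BSS = 1 – BS/BS_ref_ where BS_ref_ is the base rate for the reference class", with the Brier score being the mean squared difference between forecast and outcome.

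In the Interview and Data Collection section and the Survey Versions appendix, each participant forecasts three studies with two binary questions per study. Expert surveys 1 and 2 use different sets of three studies. The novice survey uses the set of expert survey 1.

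**The concern.** An optimist, in these predictions, is someone who gives higher probabilities of replication. Brier Skill Score measures closeness to what happened, whichever way the forecast erred. An optimist scores well when studies replicate and badly when they do not, so the sign and size of an optimism-skill correlation depend on the results of a handful of studies.

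At stake is what can be concluded about the two predictions. A true and stable link between pace-of-progress belief and optimism could be reported as greater skill, as less skill, or as no association, depending on how many of three replications succeed. The named secondary measures do not repair this: the calibration term is squared, so it loses direction, and the discrimination term as written contains no forecast value.

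**Working it through.** **Inputs.** Three studies per participant (Interview and Data Collection; Survey Versions). Brier score and Brier Skill Score as defined in Primary Analysis. The number of studies replicating, k, is not given, so every value is shown. The reference score is taken as fixed and positive for all participants answering one survey; .25 is used for illustration, and any other fixed positive value leaves the signs unchanged.

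**Step 1: the plan's own anchor.** For one question over three studies and a common forecast level p,

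BS = [k(1 - p)² + (3 - k)p²] / 3.

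At p = .5 this is [k(.25) + (3 - k)(.25)] / 3 = .25 for every k, which matches the protocol's figure for a 50-50 forecast.

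**Step 2: how the score moves with optimism.** Differentiating,

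dBS/dp = [-2k(1 - p) + 2(3 - k)p] / 3 = 2(p - k/3).

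Because BSS = 1 - BS/BS_ref, its slope has the opposite sign. More optimism raises skill only while p < k/3: never at k = 0, up to p = 1/3 at k = 1, up to p = 2/3 at k = 2, always at k = 3.

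**Step 3: values, with BS_ref = .25.** For example, at k = 1 and p = .6, BS = (.16 + 2 × .36)/3 = .2933 and BSS = 1 - .2933/.25 = -.17.

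| k of 3 | p = .4 | p = .6 | p = .8 |
|---|---|---|---|
| 0 | .36 | -.44 | -1.56 |
| 1 | .09 | -.17 | -.76 |
| 2 | -.17 | .09 | .04 |
| 3 | -.44 | .36 | .84 |

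Moving from left to right (more optimistic), skill falls in the first two rows, rises and then dips in the third, and rises in the fourth. Over all six binary events the turning point becomes k/6, with k counted out of six, and the reversal is the same.

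**Step 4: size as a correlation (simulation).** Assumptions: logit-normal forecasts, person and item standard deviations of .7 on the logit scale, a latent correlation of .30 between scale and forecaster level, three studies, one question type. The scale then correlates .26 with the mean forecast whatever the outcomes. Its correlation with skill is:

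| Mean forecast | k = 0 | k = 1 | k = 2 | k = 3 |
|---|---|---|---|---|
| .65 | -.26 | -.19 | about +.06 | +.24 |
| .50 | -.25 | -.14 | +.14 | +.25 |

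Repeated runs put the k = 2 value at mean .65 between +.05 and +.07.

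**Step 5: other assumptions.** A separate simulation used a stronger link (latent correlation .5, normal forecasts truncated to 0-1). The scale's correlation with the mean forecast was .41 to .44. Its correlation with skill for k = 0 to 3 was -.42, -.24, +.23, +.42 at mean .50; -.43, -.34, +.04, +.42 at mean .65; and -.41, -.34, -.09, +.39 at mean .75. The magnitudes depend on the assumptions; the reversal does not.

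**Step 6: pooling.** Because expert surveys 1 and 2 cover different studies, k may differ between them. By step 2 the slopes can then have opposite signs, and a pooled correlation would average them. Within one survey, mean forecast and mean of forecast minus outcome differ only by a constant, so either recovers the optimism link whatever k is.

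**The case against.** The best defence is that the protocol already separates level from skill. It ranks strata on predicted replication rates apart from forecast skill, predicts that forecasts will exceed observed replications, and plans individual calibration curves. The predictor list can be read as a mixture of predictions about level and accuracy, and the sentence naming Brier Skill Score does not call it the only response. It is true that the distinction is drawn elsewhere. But none of those signed measures is attached to the predictor tests, and the protocol does name a response for them. This is therefore a response that does not fit two of its hypotheses, rather than detail left to an analysis plan.

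Several stronger readings are tempting, and the documents do not support them:

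- **That secondary objective 2 and the stated test conflict.** They agree: both concern skill. The mismatch is between that test and two of the predictions listed beneath it.
- **That the test carries no information about optimism.** Within one survey the outcomes are common to everyone and known, so the expected direction can be worked out. At k = 0 or 3 the correlation has nearly the full size (-.26 or +.24 against .26). The footnote to this section reports little variability in the replication results, which may place the study near those extremes, but the count is not given. The loss is greatest at mixed outcomes.
- **That outcomes alone set the sign.** Trait, forecast level and outcomes set it together. If optimists score worse on studies that fail, they were worse forecasters of those studies; that is a real answer to objective 2, limited to those studies.
- **That evidence reliance as a whole is affected.** Only the methodology prediction is. The other half is about skill, and Brier Skill Score suits it.
- **That a skill association should count only if it survives adjustment for mean forecast.** Mean forecast is the route by which such a trait would act on skill. In the step 4 setting at mean .65, partial correlations after adjustment were about -.03 to -.01, so the rule would remove the effect objective 2 asks about.

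**Conclusion.** The point holds for two exploratory predictions: pace of progress, and rating replication methodology as important. The response named for them measures accuracy, while the predictions concern level. The sign change follows from the definition of the Brier score and needs no simulation. Its size does rest on assumptions: with a scale-optimism correlation of .26 and a mean forecast of .65, the skill correlation runs from about -.26 to +.24 as k goes from 0 to 3, and at k = 2 it is close enough to zero that the link would probably be missed. Neither the scale-optimism correlation nor k is given in the protocol.

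The Brier Skill Score analysis itself is sound for secondary objective 2 and for the prediction about worse and better forecasters. The primary endpoint is not touched. The correction is worth making because the mismatch could reverse or hide the predicted finding and is nearly free to remove.

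**What to change.** In Predictors of Forecast Skill:

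1. For the pace-of-progress and replication-methodology predictions only, name each participant's mean forecast probability, or mean of forecast minus outcome, as the response, stratified by or adjusted for survey version.
2. Keep Brier Skill Score for secondary objective 2 and for the prediction about worse and better forecasters. Report it by survey version and interpret it as skill on those particular studies.
3. Do not make the Brier Skill Score result conditional on adjustment for mean forecast.

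The cost is one extra regression per predictor on forecasts the study collects anyway, with no change to sample size, questionnaire or primary analysis.

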| SAMPLING  Study sampling and sample sizes:  Our study sampling frame will consist of all (approximately 35) studies being tested in the Reproducibility Project:Cancer Biology. We will categorize the studies based on theoretical and practical features. We will remove studies due to lack of feasibility (e.g. if there is not a clear relevant effect to predict, such as many in vitro studies especially those focused on cell signaling; if maturation date is too far in the future). We will prioritize studies whose results will be published sooner.  We will work with an independent expert to create or edit two to three questions for each study that can be rendered into dichotomized forecasts. In stage 1, participants will forecast all of the first six (all based on mouse models) studies from the cancer reproducibility project plans to publish. Participants will answer two binary elicitations for six events and simplified continuous elicitations for two events.  When mouse survival or tumor growth curves are used, questions will be created around them. When there are no mouse studies, we will shape a question around a study with a quantitative outcome. We plan to conduct a brief pilot to ensure the question types are relatively intuitive. Question formats might vary slightly depending on pilot results.  For the binary elicitation, our questions will take the two^[[2]](#footnote-2)^ of the following general forms:   1. How likely is it that the replication also be significant (at p ≤ .05)? 2. How likely is it that the effect size of the replication will be as large or larger than the original effect size?   For the simplified continuous elicitation (SCE) for the effect size of the specified treatment group, we will use a four question format, based on [9]:  1. What is the lowest effect size you realistically anticipate will be reported for study X?  2. What is the highest effect size you realistically anticipate will be reported for study X?  3. What is your best guess of the effect size you realistically anticipate will be reported for study X?  4. How confident are you (from 0% to 100%) that your estimated interval (lowest to highest) will include the reported effect size from study X?  Investigator sampling and planned strata:  All respondents will be at least 18 years old and will complete an informed consent.  Our primary sample will include two strata:  *a) Independent Experts*: we will create a sample of about 50 to 100 eligible independent international experts by compiling a list of authors from two searchers based on each original study undergoing replication: a) *related article* searches on PubMed and b) articles citing the original report. We will include corresponding authors and anyone who appears at least three times in any single search.  b) Novices: we will recruit a sample of about 50 to 100 medical undergraduate or upper level undergraduate biology majors, graduate students, or postdoctoral fellows at various universities via department mailing lists to participate in our study.  We will aim to include two secondary strata^[[3]](#footnote-3)^:  *c) Originators*: we will contact each co-author on each original research publication for an elicitation.  *d) Replicators*: we will contact each co-author on each replication protocol - only in cases where data collection has not yet been initiated.  Subjects will be approached through email (except non-experts, who may be approached in a class), and administered the questionnaire electronically.  Individuals will be approached up to five times before declaring them as having declined participation.  Sample size:  Our target sample size is as follows:  We will collect forecasts on 3 events in a half hour. We will collect 2 binary forecasts on 6 effects from 6 experiments + simplified continuous forecasts on overall replication rates). We will split the trial sample into two surveys to minimize the number of trials for which participants only have general expertise.  We will target 30 forecasts per participant on 6 events.  We will aim for 150 participants (50X2=100 independent experts + 50 novices) and expect a minimum of 90 (30X2=60 independent experts + 30 novices). |

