| INTERVIEW AND DATA COLLECTION  Interviews will be conducted in 2 stages:   1. Intake interview: in one 30-minute survey presented over the internet (or in person, or by paper and pencil), we will present subjects with a one-page summary sheet describing each replication study (see Appendix 2), as well as a questionnaire (see Appendix 3). Individuals will be approached using appropriate elicitation technique, whereby we first a) describe the goals of the project and how to complete the questionnaire; b) attempt to motivate good performance by explaining how scoring works; c) provide a simple warm up question (asking for a weather forecast); d) elicit replication forecasts; and e) collect additional cognitive and attitudinal measures. The questionnaire will first collect forecasts, then individual difference variables (as applicable), then demographic variables. 2. Forecasts: subjective probabilities on target experiments.    - 1. 2 binary: Significant difference and direction on 3 replication studies      2. 2 @ 4 parameter simplified continuous (best estimate, range, confidence) on overall replication rates.    1. Individual difference variables       1. Actively Open-Minded Thinking[10]       2. Pace of progress of medical research (AKA Medical Boomster-Doomster, adapted from [11])       3. Self-report of expertise for each study       4. Confidence rating of each forecast       5. Time for forecasts       6. Evidence reliance       7. Familiarity with and Anticipated Impact of Reproducibility Project       8. Estimate of perfect replication of effect sizes    2. Demographics:       1. age       2. gender       3. expertise: H index, title/rank (associate professor, full professor, etc.), number of publications, number of citations (all collected from both SCOPUS & Web of Science), nationality/region 3. Post-event Interview: Once results are available, all participants will be approached for posterior and recalled forecasts. We will collect the first set of posterior distributions when the first batch of results is published. Once all data are collected, we participants will be debriefed about study hypotheses and offered an opportunity to learn their forecast skill against the average of their peers. |

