| INCENTIVIZING GOOD PERFORMANCE  Getting good forecasts requires providing strong motivations. We will create incentives in three different ways:   1. Top scores will be posted to <http://www.translationalethics.com/forecast-scoreboard/>. We will also attempt to partner with the journal that agrees to publish our manuscript for a feature article that reports on the project, and that lists the top 5 forecasters in each expert stratum by name - provided each expert provides written consent to be de-anonymized. 2. The top two expert forecasters in each stratum will be offered awards of $200 and $50 USD, respectively. The top two novice forecasters will be offered $50 and $25, respectively. 3. We will maintain a website that lists all participants in code, and that shows each individual’s Brier skill score, and the position of their score on a distribution of brier skill scores. Individuals will be told their code so that they can check their forecast performance against others. |

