**Protocol Appendix**

**Survey Versions**

1. Expert survey 1
   1. Studies 15, 21, & 44
2. Expert survey 2
   1. Studies, 19, 29, & 39
3. Expert survey 1, incentive pilot:
   1. Studies 15, 21, & 44
   2. included option to list email for us to send C$20 Amazon gift card or donate $20 to Canadian Cancer Society
4. Expert survey 2, incentive pilot:
   1. Studies, 19, 29, & 39
   2. included option to list email for us to send C$20 Amazon gift card or donate $20 to Canadian Cancer Society
5. Novice survey 1
   1. Studies 15, 21, & 44
   2. Exclude: Editor question
   3. Include:
      1. Cancer class or lab semesters question
      2. Add email to obtain results

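### One skill ranking pools two expert surveys that share no study, so if outcomes differ between the surveys, equally skilled experts can land in different tiers

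*Protocol*

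**What the plan says.** Under SECONDARY ANALYSIS ON FORECAST SKILL, once scoring is complete, "we will also rank all individual forecasters by their Brier skill scores, and randomly select individuals within tiers of upper, middle, and lower thirds". The tiers are used to test whether combined forecasts of 2, 3, 5 and 10 low-skill forecasters "can, on average, beat the forecast of randomly selected individuals from each skill tier". The same section relates the Brier skill score to each demographic and scale variable.

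The Protocol Appendix (Survey Versions) gives expert survey 1 "Studies 15, 21, & 44" and expert survey 2 "Studies, 19, 29, & 39". The only novice version uses the survey 1 studies. SAMPLING gives the reason for the split: "We will split the trial sample into two surveys to minimize the number of trials for which participants only have general expertise". It does not mention random assignment. INTERVIEW AND DATA COLLECTION lists "2 binary: Significant difference and direction on 3 replication studies", so each person is scored on 2 × 3 = 6 binary outcomes.

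PRIMARY ANALYSIS defines the skill score as BSS = 1 − BS/BS_ref, where the reference is a base rate for a reference class or, if that is unknown, the sample variance. It does not tie the reference to a survey or a study. Under INCENTIVIZING GOOD PERFORMANCE, "The top two expert forecasters in each stratum will be offered awards"; the independent-expert stratum contains both surveys.

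**The concern.** A Brier score depends on the outcomes that happened to occur as well as on the forecaster. Two people with the same forecasting habits, scored on different studies, have different expected scores if those studies turn out differently. Ranking them on one scale then mixes skill with survey version.

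Three uses are exposed. The tier comparison would partly set one survey against the other. A trait that differs between the two expert groups, which were separated by field, could appear to predict skill. Prizes taken across the whole expert stratum on any Brier-based score would depend partly on which survey an expert received.

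**Working it through.** **Inputs from the protocol.** Six binary items per person. Sample target: "We will aim for 150 participants (50X2=100 independent experts + 50 novices"), that is, 50 experts per survey, with the 50 novices on the survey 1 studies. Plan's own figure: a constant 50-50 forecast scores .25, and (.5 − 0)² = (.5 − 1)² = .25 reproduces it.

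**Assumptions, not in the protocol.** All experts are equally skilled and draw forecasts from one distribution with mean m and SD s. Only k, the number of positive outcomes among a survey's six, differs between surveys. PRIMARY ANALYSIS expects forecasts to be more optimistic than the results, so m above .5 is plausible.

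**Expected score.** An item with outcome 0 contributes m² + s², and an item with outcome 1 contributes m² + s² + 1 − 2m. Hence

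E(BS) = m² + s² + (k/6)(1 − 2m).

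Each extra positive outcome shifts the score by (1 − 2m)/6: 0 at m = .50, −.017 at .55, −.05 at .65, −.083 at .75. With m = .65 and s² = .0325, E(BS) is .455 at k = 0, .355 at k = 2, .305 at k = 3 and .255 at k = 4. With m = .6 and s = .2 it is .40 at k = 0 and .30 at k = 3.

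**Does the skill score remove the shift?** (m = .65)

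- Common reference .25, 2 v 4 positives: 1 − .355/.25 = −.42 against 1 − .255/.25 = −.02. The raw order is kept.
- Constant 80% forecast as reference, 2 v 4: BS_ref = (2 × .04 + 4 × .64)/6 = .44 and (4 × .04 + 2 × .64)/6 = .24. BSS = 1 − .355/.44 = .19 against 1 − .255/.24 = −.06. The order reverses.
- Survey-specific sample variance p(1 − p), 2 v 3: references .222 and .25. BSS = 1 − .355/.222 = −.60 against 1 − .305/.25 = −.22. The gap remains. With k = 0 the reference is 0 and BSS is undefined.

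**Effect on tiers.** Simulation with 50 experts per survey, m = .6 to .7, s = .2, forecasts correlated within person (latent correlation .4), 400 data sets per setting, reference .25:

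| Positives of 6, survey 1 v 2 | Survey 1 share of lowest third |
|---|---|
| equal counts | 50% |
| 0 v 1 | 58-63% |
| 2 v 3 | 63-71% |
| 2 v 4 | 73-91% |
| 0 v 3 | 79-95% |

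With the 80% reference, 0 v 3 gives survey 1 67-82% of the top third; under .25 it had 23-39%.

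A second simulation (m = .65, s² = .0325, independent items, 500 data sets, reference .25) at 2 v 4 puts 13% of survey 1 experts and 55% of survey 2 experts in the upper third. Adding 50 equally skilled novices on the survey 1 studies, as the full ranking would, gives 18% of people on survey 1 studies against 64% on survey 2. At m = .50 the gap vanishes.

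**Top-two places.** In the correlated setting, survey 1 takes 81% of these at 0 v 3 (m = .6) but 15-26% at 2 v 4. The direction varies because the spread of scores changes along with the mean. Centring each squared error on the item mean still leaves survey 1 with 78-100% of top-two places when outcomes differ.

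**The case against.** Several points on the other side stand. The analysis is labelled exploratory, the primary Brier analyses do not use the tiers, and footnote 4 says that little variability in the results has already ruled out some analyses. If the two sets of studies turned out alike, the ranking is balanced. The direction and size of any distortion depend on the reference score, which the protocol leaves loose.

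A reader might infer that the tiers simply become the two surveys. That holds only for large outcome differences under a common reference; at 0 v 1 the lowest third is 58-63% survey 1. A reader might also infer that prizes come from this ranking. The incentives section names neither the prize score nor a link to the tiers; it only pools both surveys within the stratum. Nor do the documents show a trait that differs between the two expert groups, so bias in the predictor tests is a risk and not a demonstrated result. Regression covariates might properly be left to an SAP, but the single ranking and its thirds are fixed in the protocol itself.

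SAMPLING also says that participants forecast all six studies, which would make scores comparable. That conflicts with the split in the same section, with the three studies per interview and with the survey map, and the passages should be reconciled. Footnote 2 says that the text is the version implemented after piloting, and the survey map is the specific statement of what was administered.

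**Conclusion.** The concern holds, conditionally. The stated rule sorts equally skilled experts by survey whenever the two sets of studies replicate at different rates and forecasts do not centre on 50%. None of the reference scores considered cures this: a common one keeps the raw order, an 80% base rate reverses it, and a survey-specific variance leaves the gap and can be undefined. The size runs from none (equal counts) to 79-95% of the lowest third (0 v 3), under assumed forecast means, spread and outcome counts. Any Brier-based prize score pooled over the expert stratum shares the defect. Because the analysis is secondary and exploratory and the observed outcomes varied little, the realised effect may be small. The plan could not rely on that in advance, and the correction is cheap enough to be worth making.

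**What to change.** Form the ranking and the thirds within survey version, comparing novices with survey 1 experts only. Compare aggregated forecasts with individuals from the same survey. Include survey version as a covariate in the predictor-of-skill tests. Choose prize winners within survey, or on a score standardised within survey for both mean and spread; centring on the mean alone is not enough. State which reference score is used.

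This needs wording and one covariate, and no new data. The price is smaller tiers. With 50 experts in a survey each third holds about 17. At the expected minimum of 30 it holds 10, so a within-survey aggregate of 10 low-skill experts could be formed in only one way in survey 2.
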